#### Secondary endpoints

The secondary endpoints include overall mortality as well as hip function evaluated with Harris hip score (HHS) [17]. The score is widely used for evaluating hip function after THA and has also been validated as a self-reported instrument and for patients with fractures of the femoral neck [18–20]. Other endpoints includes pain when walking in the involved hip (measured with a visual analogue scale (VAS) [21] and activities of daily living (ADL) [22]. Other data collected include intraoperative bleeding, duration of surgery and vital signs (blood pressure, heart rate and pulse oximetry before, during and after stem insertion) to estimate any decrease in value during cementing. In addition, we measure serological markers of inflammation (Interleukin-6 [IL-6], C-reactive protein [CRP]) and thrombosis (D-dimer) at operative day, post-operative day (POD) 1, POD 4 and at 3 months. We will record all general medical complications including cardiovascular events and thromboembolism.

#### Radiology

Radiological analysis includes the presence of radiolucent lines around the stem and cup in the zones of Gruen et al. [23] and Delee and Charnley [24]. Any circumferential radiolucent lines around the implants will be defined as loosening. Heterotopic ossification is graded according to the classification of Brooker et al. [25]. All radiological evaluations will be done by an independent radiologist not otherwise involved in the study.

### Data collection and follow-ups

The primary assessment will establish that the patient fulfils all inclusion/exclusion criteria and identify any comorbidity. The patients will then be interviewed by a research nurse regarding living conditions, mobility, activities of daily living (ADL) [22], status and health-related quality of life according to the EQ-5D during the last week before the fracture as a baseline. For all primary and secondary endpoints including ADL the patients themselves will be providing data during the study period. It is obvious that the patients’ ability to record this correctly while awaiting urgent surgery may be questioned. It is, however, impossible to collect these data in a prospective manner and the method is regularly used in patients with a fracture of the hip [1, 2, 19]. Patients who are unable or unwilling to attend follow-ups will be interviewed by telephone or they will send their answers by mail. We will use the unique Swedish personal id-number and collect data prospectively throughout the study period through a combination of a search of our databases, follow-ups and the Swedish Hip Arthroplasty Register. Non hip-related adverse events (AEs) and serious adverse events (SAEs) will be collected throughout the study period (2 years). Although the primary endpoints will be evaluated at 2 years, the study will also include a 4 and 10-year follow-up. The study visits are presented in Table 1.

**Table 1 Tab1:** All visits in the study

	d 0	d 0	0	+1 d	+4 d	5d	3 m.	1 y	2 y	4 y	10 y
	Screening	Inclusion	Randomization and surgery	POD1	POD4	End of In-pt stay	Follow-up	Follow-up	Follow-up	Follow-up	Follow-up
Screening for eligibility	x										
Informed consent		x									
Baseline data		x									
Randomization			x								
X-ray	x			x				x	x	x	x
HHS		x						x	x	x	x
VAS		x						x	x	x	x
EQ-5D		x						x	x	x	x
Adverse events			x	x		x	x	x	x	x	x
Intraoperative			x								
Blood test		x		x	x		x				

X-ray = anterioposterior and lateral radiographs, HHS = Harris hip score, EQ-5D = Quality of life score, Intraoperative = Intraoperative measurements including blood pressure, puls rate, pulse oxyometry before, during and after femoral stem insertion, VAS = Visual Analogue Scale for hip pain, Bloodtest = C-reactive protein (CRP), IL-6, Hb, D-dimer

### Data quality assurance

The monitoring of the study and the data quality assurance will be identical to the methods published in two other study protocols from our research group [26, 27]. Briefly, we will use an external monitor to ensure that ICH- GCP [10] and all aspects of the protocol are followed. All study data will be collected and managed in a digital case report form (CRF) using REDCap electronic data capture tools hosted at Karolinska Institutet [28]. Each subject will receive a unique identification number, which will be linked to the CRF. The data will then be blinded correspondingly in all data analyses.

### Sample size and power analysis

Prior to the study start, a sample size calculation was done. To show non-inferiority with 80 % power of the primary endpoint all hip-related complications between the two groups, assuming a total complication rate of 20 %, and with a non-inferiority limit of 15 % requires 60 patients in each group. The assumed 20 % complication rate includes also minor hip-related complications as per previously published papers ranging between 10 and 20 % [1, 2, 6]. To show non-inferiority with 80 % power of the primary variable health related quality of life – HRQoL, as measured with EQ-5D requires 40 patients in each group, and with a non-inferiority limit of 0.1, assuming a value of 0.73 (SD 0.18) 1 year after the surgery [5]. The alpha (2-tailed) is set at 0.025 since we have two endpoints for the power calculation. Since this patient group has a 1-year mortality of 10 %, 70 patients in each group should be sufficient for the study.

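### The stated 60 patients per group give about 43% power for hip-related complications (70 per group about 49%), not 80%; the stated inputs need 136 per group

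*Protocol article*

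**What the plan says.** All the inputs stand in one paragraph of the protocol article, under Sample size and power analysis. The aim is given as "To show non-inferiority with 80 % power of the primary endpoint all hip-related complications between the two groups". The calculation is "assuming a total complication rate of 20 %, and with a non-inferiority limit of 15 % requires 60 patients in each group". The text then explains what the rate covers: "The assumed 20 % complication rate includes also minor hip-related complications", with published figures between 10% and 20%. The significance level follows: "The alpha (2-tailed) is set at 0.025 since we have two endpoints for the power calculation". Finally, to allow for 10% mortality at one year, the article concludes that "70 patients in each group should be sufficient for the study". Under Randomization and blinding, allocation is 1:1.

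The EQ-5D calculation in the same paragraph asks for only 40 per group, so the complication endpoint determines the trial size.

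**The concern.** The article prints a complete set of inputs and a result, and the result is less than half of what the inputs require. This cannot be put down to a condensed article leaving detail to a fuller document, because no input is missing.

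Hip-related complications are one of the two primary endpoints, and the Background hypothesis is that the uncemented stem does not cause more of them. If the two stems are truly equal at the planning rate, a trial of this size has roughly an even chance of failing to show it. Readers would then weigh an inconclusive interval against a claimed 80% power that the design never had, and could take it as evidence against the uncemented stem.

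**Working it through.** **Inputs.** From Sample size and power analysis: complication rate p = 0.20, margin d = 0.15, power 80% (z = 0.8416), two-tailed alpha 0.025, which leaves 0.0125 in the non-inferiority tail (z = 2.2414). Allocation is 1:1. One input is an assumption: the true rate is 20% in both arms. The article does not say so, but this is the usual planning assumption for non-inferiority. The rate is called total because it includes minor complications; it is not a sum over the two arms.

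**Attempt to reproduce 60.**

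n per group = (z_alpha + z_beta)² × 2p(1 − p) / d²

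= (2.2414 + 0.8416)² × 0.32 / 0.0225 = 9.505 × 14.22 = 135.2, so **136**.

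The stated 60 is not reproduced. A continuity correction moves further away, to 150.

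**Power of the planned sizes.** Power = Φ(d / SE − z_alpha), with SE = √(0.32 / n).

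- n = 60: 0.15 / 0.0730 = 2.054; Φ(2.054 − 2.241) = 0.426
- n = 63 (70 less 10%): 0.446
- n = 70: 0.15 / 0.0676 = 2.219; Φ(2.219 − 2.241) = 0.491

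Exact binomial enumeration agrees, so the normal approximation is not the cause. For 60 and 70 per group it gives 43% and 50% with Newcombe limits, 42% and 48% with the Farrington-Manning score test, and 44% and 50% with the Wald test.

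**Other readings of alpha, at a 20% rate:**

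| Alpha | n per group for 80% | Power, n = 60 | n = 63 | n = 70 |
|---|---|---|---|---|
| two-tailed 0.025 (stated) | 136 | 43% | 45% | 49% |
| one-sided 0.025 (two-tailed 0.05) | 112 | 54% | 56% | 60% |
| one-sided 0.05 | 88 | 66% | 68% | 72% |
| one-sided 0.10 | 65 | 78% | 79% | 83% |

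For 60 per group to have 80% power at this rate, the one-sided alpha would have to be 1 − Φ(2.054 − 0.842) = 0.113, about nine times the stated 0.0125 per tail. At the stated alpha, the margin would instead have to be 3.083 × 0.0730 = 22.5 points.

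**Margin that 70 per group can exclude with 80% power at a 20% rate.** 3.083 × 0.0676 = 21 points at two-tailed 0.025; 2.802 × 0.0676 = 19 points at two-tailed 0.05.

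**Low end of the article's own range (10%).** At two-tailed 0.025 the requirement is 77 per group, and power is 69% with 60, 71% with 63 and 76% with 70. At two-tailed 0.05, 70 per group gives 84%.

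**Where 60 might have come from.** Two calculations land near it. A 10% rate per arm at two-tailed 0.05 gives 63. A superiority comparison of 20% with 5% at one-sided 0.05 (pooled variance under the null) gives 60. Neither is the calculation described, and the article does not allow a choice between them.

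**The case against.** The best defence is that the headline combines the strictest reading of alpha with the least favourable event rate. The 0.025 may be a mislabelled one-sided level, and the Abstract and the Analysis section speak of 95% intervals. On that reading, 70 per group has 60% power at a 20% rate, and the chance of failure is about 40% rather than half. The 20% is also the top of the article's 10–20% range; at 10%, 70 per group gives 76% or 84%, depending on alpha. Power also depends on the equal-rates assumption: if the true rates were 20% with cement and 15% without, 70 per group would reach 81% at two-tailed 0.025.

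These points set the size of the shortfall but do not remove it. Twenty per cent is the rate the authors chose to plan on, and even one-sided 0.05 leaves 72% with all 70 evaluable. One-sided 0.10 comes close to 60, but it contradicts the stated alpha. An advantage for the uncemented stem is not what the article assumes, and its Background reports more periprosthetic fractures with uncemented implants. One adjustment goes the other way: the 49% counts all 70 per group as evaluable, whereas the article sets 70 so as to absorb 10% mortality, which leaves 63 and about 45%.

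**Conclusion.** The sample-size statement is wrong as written. With a 20% rate in both arms, a 15-point margin and two-tailed alpha 0.025, 80% power needs 136 evaluable patients per group, or 136 / 0.9 = 152 enrolled per group after the article's 10% allowance. The stated 60 gives about 43% power. The planned 70 gives about 49% if all are evaluable and 45% if 63 are. Reading alpha as two-tailed 0.05 raises the range for 60 to 70 per group only to 54–60%. The conclusion rests on equal true rates and on the 20% planning value; at 10% the shortfall is small. What produced the 60 cannot be settled from the article and does not affect the conclusion. This must be corrected, because the figure sets the size of the trial.

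**What to change.** Replace the complication part of the sample-size paragraph with a statement to this effect:

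- Assuming the same true rate of 20% in both arms, a 15-point margin and two-tailed alpha 0.025, 80% power would need 136 evaluable patients per group (152 enrolled with 10% attrition).
- The planned 70 per group gives about 49% power at a 20% rate and about 76% at 10% if all are evaluable, or about 45% and 71% with 63 evaluable.
- Non-inferiority will be judged on the two-sided 97.5% confidence interval for the risk difference, which matches the stated alpha. An interval that crosses 15 points will be reported as inconclusive.

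If the authors meant a different alpha, they should say so and use the matching row of the table above and the matching interval level. The 95% intervals in the Abstract and the Analysis section should not be left to serve as the decision rule by default.

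The cost is a rewritten paragraph and a less favourable stated power. No extra patients are needed. The rewording makes the statement correct but does not restore the power; only a larger trial would do that.

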### Randomization and blinding

The patients will be block-randomized in a 1:1 ratio, to receive either cemented or uncemented stem. We will use sealed envelopes and randomization will be stratified by sex to ensure that the sex distribution will be the same in both groups. The study subjects will be blinded to choice of treatment. To verify that the blinding is maintained during the study, the patients will be asked if they knew their assigned allocation arm at the 2-year follow-up. The surgeons and staff are not blinded during the study.

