### Outcome measurements

#### Primary endpoints

The primary endpoints will be 1) the incidence of all hip-related complications up to 2 years after surgery and 2) change in health-related quality of life assessed with EQ-5D index (EuroQol) [16] up to 2 years. Hip-related complications are defined as intra- and postoperative periprosthetic fractures, dislocation, wound infection both superficial and deep, loosening both early and late and revision of any prosthetic implant for any reason.

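### The EQ-5D sample size of 40 per group matches one-sided alpha 0.05, not the stated two-tailed 0.025 (62 to 63 needed), and the loss allowance covers one year of a two-year endpoint

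*Protocol article*

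**What the plan says.** The Sample size and power analysis section treats EQ-5D as one of two primary variables and gives it its own calculation: "To show non-inferiority with 80 % power of the primary variable health related quality of life", it says, "as measured with EQ-5D requires 40 patients in each group, and with a non-inferiority limit of 0.1, assuming a value of 0.73 (SD 0.18"). The SD is a one-year value: "assuming a value of 0.73 (SD 0.18) 1 year after the surgery". The error level for both calculations is given as: "The alpha (2-tailed) is set at 0.025 since we have two endpoints for the power calculation". The step from the calculated sizes to the planned size is: "Since this patient group has a 1-year mortality of 10 %, 70 patients in each group should be sufficient for the study".

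The endpoint itself lies at two years. The Primary endpoints section defines it as "change in health-related quality of life assessed with EQ-5D index (EuroQol) [16] up to 2 years", and Data collection and follow-ups says: "Although the primary endpoints will be evaluated at 2 years, the study will also include a 4 and 10-year follow-up". Allocation is equal: "The patients will be block-randomized in a 1:1 ratio".

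**The concern.** The sample size paragraph gives the margin, SD, power and alpha, so its 40 can be checked directly. It looks too small for an alpha that has been halved for two endpoints and is two-tailed as well. Separately, the only allowance for loss is a one-year mortality, while the patients must supply EQ-5D data at two years.

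The two points combine. Set against 40, the 63 patients per group left after 10% loss look like ample cover. If the true requirement is about 63, there is no cover at all, and every further death or non-response in year 2 lowers the power below the stated 80%. Readers of an inconclusive non-inferiority result would rely on that stated power to interpret it.

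**Working it through.** **Inputs.** Margin 0.1, SD 0.18, power 80%, alpha 0.025 two-tailed, 70 randomised per group and 10% loss all come from Sample size and power analysis. Allocation is 1:1 (Randomization and blinding). The protocol gives no true difference, so I assume 0, the usual choice for non-inferiority. A non-inferiority test uses one tail, so two-tailed 0.025 means 0.025 / 2 = 0.0125 in the direction that matters.

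**Formula.** n per group = 2 × SD² × (z_alpha + z_power)² / margin² = 2 × 0.0324 / 0.01 × (z_alpha + z_power)² = 6.48 × (z_alpha + z_power)², with z_power = 0.8416.

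| One-sided alpha | z_alpha | n per group (normal) | n per group (t) |
|---|---|---|---|
| 0.05 | 1.6449 | 6.48 × 2.4865² = 40.06 | 41 |
| 0.025 | 1.9600 | 6.48 × 2.8016² = 50.86, so 51 | 52 |
| 0.0125 (as stated) | 2.2414 | 6.48 × 3.0830² = 61.59, so 62 | 63 |

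The first row reproduces the protocol's 40, apart from rounding up. Neither reading of 0.025 does.

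**Power with 40 per group at the stated alpha.** The standard error is 0.18 × √(2/40) = 0.04025, and 0.1 / 0.04025 = 2.4845. Subtracting 2.2414 leaves 0.243, which gives 59.6% (58.0% with the noncentral t).

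**What 70 per group leaves.** With the protocol's 10% loss, 70 × 0.90 = 63. If 10% were lost in each of two years (my assumption), 70 × 0.81 = 56.7, or about 57. Over a range of two-year loss from 12% to 20%, between 70 × 0.88 = 61.6 (about 62) and 70 × 0.80 = 56 remain.

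| Evaluable per group | Loss from 70 | Power, normal | Power, t |
|---|---|---|---|
| 70 | 0% | 85.2% | 84.5% |
| 63 | 10% | 81.0% | 80.1% |
| 62 | 11.4% | 80.3% | 79.4% |
| 60 | 14.3% | 78.9% | 77.9% |
| 57 | about 19% | 76.6% | 75.5% |
| 56 | 20% | 75.8% | 74.7% |

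The apparent reserve is 63 − 40 = 23 per group. The real one is 63 − 63 = 0 with the t distribution, or 63 − 62 = 1 with the normal approximation.

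**The case against.** The arithmetic is hard to dispute. The case on the other side is about consequence, and parts of it stand.

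- **EQ-5D did not set the trial size.** The 70 per group come from the complications endpoint (60, raised for mortality). On the protocol's own 10% loss, EQ-5D still just reaches 80%. This is correct, and it is why the conclusion is that power is not assured rather than that the trial is underpowered for EQ-5D.
- **The two-year loss is not given.** Also correct. The 57 per group is an illustration, and the drop it produces is about 4 to 5 percentage points.
- **The alpha could be read more leniently.** The Abstract and the Analysis section refer to 95% confidence intervals, which imply one-sided 0.025. The need would then be 51 to 52 per group, t-based power would be 87% at 63 and 84% at 57, and about 26% loss could be absorbed (1 − 52/70). The loss problem would largely disappear, but 40 would still be wrong, and the sample size section explicitly states two-tailed 0.025.
- **Missing EQ-5D values are carried forward, and telephone or mail contact is planned.** This may keep patients in the analysis, but the protocol itself counts deaths as loss when it inflates the sample. A carried-forward value adds no two-year information. Table 1 has no EQ-5D at 3 months, so a patient lost before one year has only the recalled pre-fracture value to carry forward.
- **The SD of 0.18 is itself a one-year value, and the endpoint is a change score whose SD is not given.** This stands: 63 is conditional on 0.18.
- **The 60 for complications is itself doubtful.** With 20% in both groups and margin 0.15, n = (z_alpha + z_power)² × 2 × 0.2 × 0.8 / 0.15² gives 88, 112 and 136 per group at one-sided 0.05, 0.025 and 0.0125. That is a separate matter. It means nothing here should be taken as confirming that 140 patients suffice for that endpoint.

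**Conclusion.** The concern holds. The 40 per group contradicts the alpha given in the same paragraph: the requirement is 62 to 63, and 40 gives 58% to 60% power. The loss allowance covers one year of a two-year endpoint. Together these hide the fact that 70 randomised per group give EQ-5D about 80% power only if no more than about 10% to 11% are lost by two years. At an assumed 19% loss, power is about 76%. These figures rest on a true difference of 0, an SD of 0.18 at two years and alpha read as written. The error should be corrected because it concerns the stated power of a co-primary endpoint, but on the protocol's own inputs the shortfall is modest and conditional.

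**What to change.** Reword two sentences in Sample size and power analysis.

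1. Replace the EQ-5D figure of 40 by 63 evaluable patients per group, stating that it assumes two-tailed alpha 0.025 (0.0125 in the non-inferiority direction), a true difference of 0 and an SD of 0.18 taken from one-year data.
2. Replace the one-year mortality by an expected loss to two years, covering deaths and non-response, and give the resulting EQ-5D power for 70 randomised per group: about 80% if 63 are evaluable and about 76% if 57 are.

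On this point the total of 140 can stay. The cost is the rewording and slightly less favourable stated figures; no extra patients or procedures are needed.

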## Background

Total hip replacement (THR) is the preferred method for the active and lucid elderly patient with a displaced femoral neck fracture (FNF) [1, 2]. Comparisons between cemented and uncemented stems in hip arthroplasty for patients with a FNF have almost consistently favoured cemented fixation, mainly because of greater deterioration in pain, walking ability, use of walking aids and activity of daily living [3] and because of a higher incidence of hip related complication such as periprosthetic fracture [4] for uncemented implants. Despite this, recent reports on modern, hydroxyapatite-coated femoral stems used for this patient-group have shown promising early results [5-7]. In addition, bone cement implantation syndrome (BCIS), is more prevalent in cemented than in uncemented stems [8]. It is also a commonly occurring phenomenon in patients treated for FNF with cemented arthroplasty and severe BCIS has a significant impact on early and late mortality [9]. Thus, the use of uncemented stems for this patient group may still be justified.

We hypothesized that an uncemented, proximally porous and hydroxyapatite coated femoral stem used in THR for a displaced FNF would not be associated with more adverse peri- and postoperative hip-related complications compared with a THR using cemented stem, and that the health-related quality of life for the patients would be equivalent at 2 years.

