### Analysis

Analyses of outcome are based on the intention-to-treat principle and all patients remain in their randomized group regardless of any further surgical intervention. Patients with missing data (i.e. EQ-5D, HHS VAS etc.) at any of the follow-ups are analysed with the last observation carried forward (imputed). Descriptive statistics (means and standard deviations) will be used to describe the patient characteristics and outcome variables at the measurement points. Fisher’s exact test will be used to test the primary endpoint. We will use the Student’s *t*-test and Levene’s test for comparison of the functional outcomes with 95 % CI presented. We will use Kaplan-Meier survival curves with log-rank test for patient and hip re-operation survival analysis. The analyses will be performed with SPSS 22.0 for Mac (SPSS, Chicago, Illinois) statistical software.

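### The two-tailed alpha of 0.025 set for the two primary endpoints is not carried into the analysis, which refers only to 95 % intervals, and no rule says whether one or both endpoints must succeed

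*Protocol article*

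**What the plan says.** **Level.** The section Sample size and power analysis says: "The alpha (2-tailed) is set at 0.025 since we have two endpoints for the power calculation". It covers two non-inferiority comparisons:

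- Complications: the aim is worded as "To show non-inferiority with 80 % power of the primary endpoint all hip-related complications between the two groups". The planning rate is 20 % and the limit is 15 percentage points, for which the article gives 60 per group.
- EQ-5D: the planning value is 0.73 (SD 0.18) at one year and the limit is 0.1. The article's figure is worded as "as measured with EQ-5D requires 40 patients in each group".

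The total is then set at 70 per group to allow for 10 % one-year mortality.

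**Analysis.** The Abstract says that results will be analysed with 95 % confidence intervals for the effect size. The Analysis section assigns Fisher's exact test to the primary endpoint without a significance level. It names the t-test and Levene's test for a further set of outcomes, in these words: "for comparison of the functional outcomes with 95 % CI presented". Neither place mentions a 97.5 % interval or a 0.025 test level.

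**Hypothesis.** The Background states one hypothesis with two parts. The first is that the uncemented stem would not bring more hip-related complications. The second follows in the same sentence: "compared with a THR using cemented stem, and that the health-related quality of life for the patients would be equivalent at 2 years". The section on primary endpoints lists the two endpoints but does not say whether one or both must succeed.

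**The concern.** Three statements do not fit together. The alpha split is a correction for claiming success on either endpoint. The Background hypothesis joins the endpoints with 'and', which suggests that both are needed. The analysis uses the interval level that applies when there is no split.

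A result that meets a limit on a 95 % interval but not on a 97.5 % interval, or that meets only one of the two limits, could therefore be reported as non-inferiority or not. Each reading could cite the protocol, and the choice could be made after the data are seen. At stake are the type I error of the claim under one rule and its power under the other.

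**Working it through.** **Inputs (Sample size and power analysis).** Two-tailed alpha 0.025, so 0.0125 in the one tail that matters for non-inferiority. Power 80 %. Complication rate 20 %, limit 15 percentage points. EQ-5D SD 0.18, limit 0.1. 70 per group less 10 % gives 70 × 0.9 = 63 evaluable.

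**Assumptions.** 20 % complications in both arms, no true EQ-5D difference, the one-year mortality figure used as the total loss for both endpoints, and independence of the endpoints wherever they are combined.

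**1. The plan's own figures.** Normal approximation, per group:

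- Complications: n = (z₁₋α + z₀.₈)² × 2 × 0.2 × 0.8 / 0.15²
- EQ-5D: n = 2 × (z₁₋α + z₀.₈)² × (0.18 / 0.1)²

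| One-sided level | Matching two-sided interval | (z₁₋α + z₀.₈)² | Complications (× 14.222) | EQ-5D (× 6.48) |
|---|---|---|---|---|
| 0.0125 (as stated) | 97.5 % | (2.241 + 0.842)² = 9.505 | 136 | 62 |
| 0.025 | 95 % | (1.960 + 0.842)² = 7.849 | 112 | 51 |
| 0.05 | 90 % | (1.645 + 0.842)² = 6.183 | 88 | 41 |
| Stated in the plan | | | 60 | 40 |

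The stated 60 and 40 do not follow from the stated alpha. Only the 40 is approximately recovered, and only at one-sided 0.05. That is a separate sample-size issue. It matters here only because it means the split cannot be seen in the planned numbers either.

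**2. Error if either endpoint suffices.**

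- 95 % intervals (one-sided 0.025 each): 1 − (1 − 0.025)² = 0.0494. Without independence the bound is 2 × 0.025 = 0.05.
- 97.5 % intervals (one-sided 0.0125 each): 1 − (1 − 0.0125)² = 0.0248. The bound is 0.025.

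**3. Error if both endpoints are required.** A false claim of non-inferiority on both needs a false rejection on at least one endpoint whose null is true. The error is therefore at most the level of a single test. With 95 % intervals this is 0.025 one-sided, with no split.

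**4. Power at 63 per group.**

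- Complications: standard error √(0.32 / 63) = 0.0713, and 0.15 / 0.0713 = 2.105. Power is Φ(2.105 − 1.960) = 0.558 at 95 % and Φ(2.105 − 2.241) = 0.446 at 97.5 %.
- EQ-5D: standard error 0.18 × √(2 / 63) = 0.0321, and 0.1 / 0.0321 = 3.118. Power by the non-central t is 0.872 at 95 % and 0.801 at 97.5 %. The normal approximation gives 0.877 and 0.810.
- Both endpoints together: 0.558 × 0.872 = 0.487 at 95 %, and 0.446 × 0.801 = 0.357 at 97.5 %.
- At least one endpoint at 97.5 %: 1 − (1 − 0.446) × (1 − 0.801) = 1 − 0.554 × 0.199 = 0.890.

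**The case against.** **The text does not say that the limits will be compared with 95 % intervals.** The Analysis section attaches them to functional outcomes, complications get Fisher's exact test without a level, and the broader statement is in an Abstract. Presenting a 95 % interval does not by itself fix the test level, and a separate analysis plan may settle it. This stands as a caution about wording. But the Abstract's statement covers the results in general, so the article gives two levels that do not match. That is a conflict between stated figures, not only a missing detail.

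**The 0.025 may have been meant as a one-sided level, which would match a 95 % interval.** The sentence does not support this: it calls the alpha two-tailed and explains the value by the number of endpoints.

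**A reader might infer that the trial must either lose control of its error rate or give away power.** The documents do not support that. With 95 % intervals and both endpoints required, the one-sided error is at most 0.025 and no power is lost. The remaining defect would be a superfluous sentence on alpha. Equally, the both-required rule is an inference from one conjunction in the Background. The split itself hints that either endpoint might be claimed, and it is valid, if conservative, under both rules.

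**A reader might also blame the split for the low power on complications.** That does not hold either. Without the split, power is still about 56 % against a target of 80 %, because 112 evaluable per group would be needed. The shortfall comes mainly from the sample-size arithmetic. For EQ-5D, power with the split is about 80 %, which meets the target.

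**Conclusion.** The point holds as an inconsistency of level combined with an unstated success rule. The stated alpha implies 97.5 % intervals, and the analysis refers only to 95 % intervals.

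- **Either endpoint may be claimed:** the one-sided family-wise error with 95 % intervals is about twice that of the stated split.
- **Both endpoints are required:** the split serves no purpose. Applying it would cost about 11 percentage points of power on complications and 7 on EQ-5D.

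The documents do not show which case applies, so neither inflated error nor lost power is established as a fact about this trial. The power figures rest on 63 evaluable per group and the planning values. They would change with losses over two years, or if deaths still contributed complication data.

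**What to change.** State the success rule and use one level in the sample-size section, the Analysis section and the Abstract. Two consistent versions are available:

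1. **Either endpoint may support a claim.** Keep the two-tailed 0.025. Judge each primary endpoint on a two-sided 97.5 % interval against its limit (15 percentage points for complications, 0.1 for EQ-5D).
2. **Both endpoints are required.** State that non-inferiority is declared only if both limits are met, each on a two-sided 95 % interval, and delete the alpha split.

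The second version is closer to the Background hypothesis, but the choice belongs to the investigators and should be made before any outcome comparison by arm.

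**Cost.** About one sentence in each place; the change itself adds no patients or procedures. Version 1 widens the primary intervals by about 14 % (2.241 / 1.960 = 1.14). Version 2 gives up any claim on one endpoint alone and has joint power of only about 49 % under independence. Version 1 has about 89 % power to succeed on at least one endpoint, but that is a weaker claim. Neither version repairs the 60 and 40 per group, which need to be recalculated separately at whichever level is chosen.
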